## Background

The frequent co-occurrence of depression and substance use disorders (SUDs) is well documented both in Australia and internationally [1–9], with epidemiological studies suggesting that affective disorders are up to 4.7 times more prevalent among substance dependent samples compared to the general population [10–12]. Particular cause for concern is the high prevalence of current major depression among treatment seeking substance users, with studies reporting rates as high as 20–55 % [2, 4, 13–15]. Despite evidence that depression is linked to poorer treatment outcomes [16–20], the development and assessment of behavioural interventions for depression among substance users has received little empirical attention.

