#### Sample size calculation

Power analysis on the primary outcome variables (i.e., severity of dependence and depressive symptoms) was conducted using Power Analysis and Sample Size software [53]. Based on previous research, including the longitudinal study of treatment outcomes for heroin dependence (ATOS; [20]), an exchangeable working correlation matrix and a within-subject correlation of ρ^1^ = .60 for dependence and ρ^1^ = .023 for depression was assumed. The proposed final sample size of 160 will allow for the detection of clinically meaningful differences between the treatment and control groups. Specifically, it will allow for the detection of a time-averaged difference of 3 in severity of substance dependence with a standard deviation of 5 (β = 99 % power; *α* = 0.05); a 15 % difference in the prevalence of substance dependence (β = 96 % power; *α* = 0.05); a difference of 5 in BDI-II scores with a standard deviation of 15 (β = 81 % power; *α* = 0.05); and a 15 % difference in the prevalence of major depression (β = 93 % power; *α* = 0.05). To allow for an expected attrition rate of 20 %, the initial sample will be 200, with the aim of recruiting 50 % of participants from RR and 50 % from OST.

Participants will be 18 years of age or older, literate in English, willing to give locator information, and must have been in RR for at least 1 week or OST for at least 3 months. RR clients must have used a substance (i.e., alcohol, methamphetamines, cannabis, cocaine, hallucinogens, illicit benzodiazepines, heroin or other opiates/opioids) at least four times in the month prior to detoxing, and OST clients must have used a substance at least four times in the past month. If alcohol is the only substance used, individuals need to have consumed four or more standard drinks on at least 4 days in the month before detoxing/past month. The depression screening criteria from the Composite International Diagnostic Interview 3.0 (CIDI; [54, 55]) must be endorsed, indicating that the individual has experienced symptoms of depression that persisted for 2 weeks or longer in the month before detoxing/past month, and these symptoms must be ongoing. Depression symptom severity will be assessed using the Patient Health Questionnaire (PHQ-9; [56]), with a score in the mild to severe range (i.e., 5–27) required to be eligible for the study.

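### The 96% power for substance dependence is given without a prevalence, and on the plan's own inputs it needs one arm within about 2–3 points of 0% or 100%

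*Protocol article*

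**What the plan says.** The Sample size calculation section bases its power figures on an exchangeable correlation structure, with a within-subject correlation of .60 for dependence and .023 for depression. It then says: "The proposed final sample size of 160 will allow for the detection of clinically meaningful differences". The 160 is a total: "To allow for an expected attrition rate of 20 %, the initial sample will be 200".

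Four power figures follow: 99% for a time-averaged difference of 3 in dependence severity (SD 5), 81% for a BDI-II difference of 5 (SD 15), and one for each CIDI diagnosis. The dependence diagnosis is given 96% for a 15-point "difference in the prevalence of substance dependence", at alpha 0.05. The depression diagnosis is given 93% for a 15-point "difference in the prevalence of major depression".

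Neither binary figure comes with a prevalence, a number of repeated measurements or a statement of sidedness. The trial registration table lists both CIDI diagnoses among the primary outcomes, and says that recruitment is completed and analysis is ongoing. The Assessment occasions section sets follow-up at 3 and 12 months after baseline.

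**The concern.** The variance of a proportion depends on the proportion. A 15-point difference is much easier to detect near 0% or 100% than near 50%, so a power figure without a prevalence cannot be checked and may rest on a favourable choice.

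The 96% is high for 80 per arm with correlated repeat measurements, so it matters which prevalences could produce it. If the true values lie in the middle of the range, a non-significant result on a primary outcome would be read as strong evidence against a 15-point effect, although the trial had a substantial chance of missing one.

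**Working it through.** **Inputs.**
- Analysed sample: 200 × 0.8 = 160, split 1:1 (Trial design), so n = 80 per arm.
- Correlation .60 for dependence and .023 for depression; alpha 0.05; d = 0.15 (Sample size calculation).
- Assumptions, because the text is silent: two-sided test; a time-averaged contrast, which the section names for severity; m = 2 measurements (3 and 12 months) or m = 3 (baseline counted).

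**Formula.** Effective number per arm: N = n·m / [1 + (m − 1)ρ].
- Dependence: 160/1.6 = 100 (m = 2); 240/2.2 = 109.1 (m = 3).
- Depression: 160/1.023 = 156.4 (m = 2); 240/1.046 = 229.4 (m = 3).

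**Does this method fit the plan?** For a mean, power = Φ(d·√(N/2)/SD − 1.96).
- Dependence severity, d = 3, SD 5: m = 2 gives Φ(4.243 − 1.96) = 98.9%; m = 3 gives Φ(4.431 − 1.96) = 99.3%. The stated 99% reproduces.
- BDI-II, d = 5, SD 15: m = 2 gives Φ(2.948 − 1.96) = 84%; m = 3 gives Φ(3.570 − 1.96) = 95%. The stated 81% is nearer m = 2.

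**Dependence prevalence.** With p₂ = p₁ + 0.15 and p̄ their mean, power = Φ(z), where

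z = [d√N − 1.96√(2p̄(1 − p̄))] / √(p₁(1 − p₁) + p₂(1 − p₂)).

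Worked for m = 2:
- 1.8% v 16.8%: z = (1.500 − 0.805)/0.397 = 1.75, power 96.0%.
- 42.5% v 57.5%: z = (1.500 − 1.386)/0.699 = 0.163, power 56.5%.

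| Arms | m = 2 | m = 3 |
|---|---|---|
| 1.8% v 16.8% | 96.0% | 97.3% |
| 2.7% v 17.7% | 94.5% | 96.0% |
| 5% v 20% | 90.0% | 92.3% |
| 10% v 25% | 80.2% | 83.5% |
| 15% v 30% | 72.2% | 75.9% |
| 25% v 40% | 62.1% | 65.9% |
| 42.5% v 57.5% | 56.5% | 60.2% |
| 55% v 70% | 59.2% | 63.0% |

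The table mirrors at the top end: 83.2% v 98.2% gives 96.0% with m = 2, and 82.3% v 97.3% gives 96.0% with m = 3.

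Simulated correlated binary data agree in the middle (57% and 60% at 42.5% v 57.5%). At the extremes they are slightly more favourable, but still below 96% at 5% v 20% (92.0% and 94.5%). Reaching 96% at 20% v 35% would take about 386 (m = 2) or 354 (m = 3) analysed participants.

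**Major depression.** The same formula with correlation .023 reaches 93% at about 11% v 26% (or 74% v 89%) with m = 2, and at about 25% v 40% with m = 3. With m = 3 it never falls below about 90%; with m = 2, 40% v 55% gives 76%.

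**The case against.** **The 96% is attainable, so nothing is contradicted.** This stands. The figure is not impossible, and the documents give no expected prevalence of dependence at follow-up. They do not strictly exclude an arm near 100% in people being treated for substance use. A reader might infer that the authors made an arithmetic slip or assumed something absurd, and the text does not support that. What can be said is narrower. The figure needs an extreme prevalence that is neither stated nor justified. Eligibility rests on use at least four times in a month, not on a dependence diagnosis; the outcome is past-month dependence; and every participant, controls included, is in treatment.

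**A condensed article may leave an input to the full protocol.** That would excuse a missing detail. Here the article prints the power itself, along with the difference, correlation, sample size and alpha, and omits the one quantity that decides the result.

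**Other calculations are more favourable.** They are, but they do not rescue the figure:
- A one-sided test moves the 96% point only to about 4–5%, and the mid-range minimum is then 69–72%.
- Taking 160 per arm reaches 96% at about 14–16% in the lower arm, but contradicts 200 less 20%.
- Using the depression correlation of .023 for dependence reaches 96% at about 8% (m = 2) or 18% (m = 3), but is not what the section says.
- Adjusting the mean of two follow-ups for baseline gives 82–93% in the middle range. The planned mixed or marginal models may gain something of this kind, so 57–76% is not the least power that the final analysis could have. But the section describes a plain time-averaged difference, and that formula already reproduces its 99%.

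**The major-depression figure may be sound.** This also stands. With three occasions, 93% falls at about 25% v 40%, within the 20–55% that the Background reports for current major depression in treatment seekers ("Particular cause for concern is the high prevalence of current major depression among treatment seeking substance users").

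**Conclusion.** The point holds for substance dependence. On the section's own inputs, 96% power requires one arm within about 2–3 points of 0% or 100%. From 15% v 30% to 55% v 70%, power is about 57–72% with two follow-ups and 60–76% with three occasions, so the chance of missing a 15-point difference is roughly 24–43% rather than 4%. This assumes 80 per arm, a two-sided test, and an unadjusted time-averaged contrast with exchangeable correlation .60.

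Two stronger conclusions are tempting and do not follow:
- That the 93% for major depression must also be replaced. It is attainable at ordinary prevalences if three occasions were used. What is open is the number of occasions, because the BDI-II figure of 81% sits nearer two (84%) than three (95%), and with two the 93% needs about 11% v 26% or 74% v 89%.
- That the CIDI diagnoses should become secondary outcomes. An unstated prevalence does not justify that, and changing registered primary outcomes after recruitment has closed carries its own risk of bias.

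**What to change.** For dependence, state the prevalence assumed in each arm, the number of occasions and the sidedness of the test. Replace the single 96% with power over a plausible prevalence range, which on the present inputs is about 57–76% in the middle. If a value near 0% or 100% was intended, give its source. In the results paper, interpret a null dependence result from the estimate and its confidence interval, not against 96%.

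For major depression, state the prevalence and number of occasions behind the 93%, and make the number consistent with the one behind the BDI-II figure.

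Leave both CIDI diagnoses as primary outcomes. The change is to wording and figures only: no further participants or data are needed. The cost is a less favourable printed power for dependence.

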### Study procedure

#### Sample site recruitment

Participants will be recruited from RR services and OST clinics in greater Sydney metropolitan area, the Central Coast, and Hunter New England Health regions. Management staff will be contacted by the project coordinator to determine their initial interest in being involved. A letter outlining the purpose of the trial, and what will be required of the agency should they choose to participate, will be sent to the services. On confirmation of intent to participate, the research team will meet with the staff to discuss logistics, and recruitment of study participants will commence.

#### Screening

Staff in the RR and OST services will inform clients that the University of New South Wales is conducting a study examining mood and substance use. They will direct those interested in hearing about the study and being screened for eligibility, to one of the project’s research officers who will be on-site to conduct the screening to help maximise recruitment. Informed written consent will then be sought by the research officers from eligible clients interested in participating, locator information to facilitate follow-up will be collected, and the baseline interview conducted. The research officers (honours graduates in psychology) have been trained in the assessment interview by the investigators (MT, JR and KM). Participants will be informed that they are free to withdraw from the study at any stage. Recruitment will occur in ten treatment services over a period of 18 months. The locations of the treatment services are listed in the Australian and New Zealand Clinical Trials registry.

#### Assessment occasions

The structured baseline interview will be administered by the research officers, followed by randomisation of participants to one of two groups; (1) TAU, or (2) Activate plus TAU (Fig. 1). The allocation sequence will be computer-generated by someone independent of the Activate team. The project coordinator will then inform the psychologist about the allocation, and they will notify the study participant. Follow-up interviews for the Activate and TAU groups will parallel each other, conducted at 3-months and 12-months post-baseline. Primary and secondary outcome measures will be assessed at all three assessment occasions, with the exception of client satisfaction, which will be assessed on completion or cessation of the Activate intervention. Follow-up interviews will be administered by the project’s research officers who will be blind to group allocation. The baseline and follow-up interviews are estimated to take 60–90 min to complete. Participants will be reimbursed AU$30 per interview for out of pocket expenses.

**Fig. 1 Fig1:**
[figure not shown]
Flow Diagram of Trial Progression

#### Locator information

A locator form will be used to record participant information that may be used to facilitate follow-up. This information will be collected at baseline and updated on both follow-up occasions. Consent to the study also provides permission for researchers to locate the participant by various means, such as social media, telephone directories, court lists, electoral rolls, and treatment services. These methods are based on those used in ATOS which achieved follow-up rates of 89, 80, 76, and 70 % at 3-, 12-, 24-, and 36-month follow-ups respectively [58].

#### Data management

To maintain confidentiality of participant data, all participant information will be stored in locked filling cabinets at the National Drug and Alcohol Research Centre, with access restricted to the research team. All records that contain names or other personal identifiers (such as locator forms and consent forms), will be stored separately from questionnaires, which will be identified by a participant identification number. All local databases will be secured with password protected access systems. Data entry will be conducted by the research officers. To maximise accuracy and consistency of data entry, a data dictionary will be used to define the variables and specify how they are to be coded. To promote data quality value range checks and consistency checks will be performed.

### Measures

#### Baseline and follow-up interviews

The baseline and follow-up interviews will examine demographics, drug use history, treatment history (for substance use and depression), and will use validated instruments to assess a) the primary treatment outcomes of depression and substance dependence, and b) secondary treatment outcomes related to the therapy and mental health. Demographic measures will include age, gender, level of education, employment status, main source of income, marital status, living arrangements, and prison history. A drug use history (including age of first use, and the number of days used in the last 30 and 90 days), will be obtained for heroin, other opiates, methamphetamine, cocaine, hallucinogens, antidepressants, benzodiazepines, alcohol, cannabis, inhalants and tobacco. Prescription drug use will also be recorded. Drug treatment and depression treatment history will assess current treatment(s), the age at which they first sought treatment, number of times they have commenced treatment, and the recency of these treatments. Information will also be obtained on the participants’ history of suicide, self-harm, and occasions where they lost consciousness as the result of a head injury.

#### Primary outcome measures

Depression: The severity of depression symptoms in the past 2 weeks will be assessed using the 21-item Beck Depression Inventory (BDI-II; [49]). Each item comprises a list of four statements arranged in increasing severity about a particular symptom of depression. Scores range from 0 to 63, with higher total scores indicating more severe depressive symptoms. Depression can then be interpreted as minimal (0–13), mild (14–19), moderate (20–28), or severe (≥29). The BDI-II has been widely used in both clinical and non-clinical studies, has shown good test-retest reliability (Pearson’s *r* = .73-.96), and high internal consistency (Chronbach’s α = .83-.96) [59]. A past month diagnosis of major depression will be ascertained by completing the CIDI 3.0 depression section, modified to assess the presence of symptoms in the past month [54, 55]. The CIDI 3.0 major depression module has been found to have moderate concordance with the Structured Clinical Interview for DSM (SCID) (area under the receiver operator curve; AUC = 0.75) [60].

Substance Dependence: Psychological components of dependence will be measured using the Severity of Dependence Scale (SDS; [61]). Each of the 5 items is scored on a 4-point scale, ranging from 0 to 3. A total score is obtained, with higher scores indicating a higher level of dependence. The inter-item reliability has been demonstrated across five drug using samples, with Cronbach’s alpha values ranging between 0.8 and 0.9 [61]. A diagnosis of substance dependence will be established using the CIDI 3.0, with the number of dependence criteria endorsed (0–7) being used as an indicator of severity [54]. The CIDI 3.0 substance use disorder module has been found to have moderate concordance with the SCID (Alcohol dependence, AUC = 0.72; Drug dependence, AUC = 0.62) [60].

Problematic alcohol use will be screened for using the 4-item CAGE questionnaire [62]. Scores range from 0 to 4, with scores greater than or equal to 2 considered to be clinically significant. The CAGE has demonstrated high test-retest reliability (*r* = 0.80–0.95), and adequate correlations (*r* = 0.48–0.70) with other screening instruments such as the Alcohol Use Disorders Identification Test (AUDIT) and Short Michigan Alcohol Screening Test (SMAST) [63].

#### Symptom monitoring and secondary outcome measures

The Patient Health Questionnaire-9 (PHQ-9) will be used in the initial screening interview, and then by therapists to monitor depressive symptoms among the intervention group [56]. The PHQ-9 is a nine-item screener for major depression and a measure of depression severity, which assesses the presence of each of the nine DSM-IV criteria for major depression in the preceding 2 weeks. Scores range from 0 to 27, as each of the nine items can be scored from ‘0’ (not at all) to ‘3’ (nearly every day) [56]. Major depression is indicated if 5 or more of the 9 depressive symptom criteria have been present at least “more than half the days” in the past 2 weeks, and 1 of the symptoms is depressed mood or anhedonia. The PHQ-9 has demonstrated excellent internal reliability (Chronbach’s α = 0.86–0.89), and test-retest reliability (*r* = 0.84) [56]. Criterion validity has been demonstrated in a sample of 580 primary care patients who were independently re-interviewed by a mental health professional. Receiver Operator Curve (ROC) analysis showed that the area under the curve for the PHQ-9 in diagnosing major depression was 0.95, suggesting that it discriminates well between persons with and without major depression [56].

Client satisfaction will be assessed after completion of Activate therapy using the Client Satisfaction Questionnaire, an 8-item scale designed to measure and assess client satisfaction with health and human services (CSQ-8; [64]). The CSQ-8 elicits the client’s perspective on the value of services received. Responses are given on a 4-point Likert scale. Scores range from 8 to 32, with higher scores indicating greater satisfaction. The CSQ-8 has demonstrated excellent reliability and internal consistency (Cronbach’s alpha 0.92 to 0.93) [64]. Secondary outcome measures, including those associated with behavioural activation therapy and mental health will be assessed at baseline, 3- and 12-month follow-up (Table 2).

**Table 2 Tab2:** Schedule of assessments

Domain	Measure	Screening	Baseline Pre-allocation	3 month follow-up	12 month Follow-up
*Eligibility*					
Depression symptoms	Patient Health Questionnaire (PHQ-9) [56]	+	−	−	−
Depression screener	CIDI 3.0 Depression screener questions [54, 55]	+	−	−	−
*Primary outcome measures*					
Substance dependence	CIDI 3.0 Substance dependence (past month DSM-IV TR) [54] Severity of Dependence Scale (SDS) [61]	− −	+ +	+ +	+ +
Depression	CIDI 3.0 Major depression (past month DSM-IV TR) [54, 55] Beck Depression Inventory-II (BDI-II) [49]	− −	+ +	+ +	+ +
*Secondary outcome measures*					
Behavioural activation	Behavioural Activation for Depression Scale Short Form (BADS-SF; [70])	−	+	+	+
Anxiety	Beck Anxiety Inventory (BAI; [71])	−	+	+	+
Social phobia	CIDI 3.0 Social Phobia (past month DSM-IV-TR) [54] Liebowitz Social Anxiety Scale [72, 73]	− −	+ +	+ +	+ +
Traumatic events & trauma symptoms	PTSD trauma checklist from the CIDI 3.0 [54] and the Post-Traumatic Stress Disorder Checklist – Civilian Version (PCL-C; [74])	-	+	+	+
Borderline Personality Disorder	International Personality Disorders Examination (IPDE; [75])	−	+	+	+
Environmental Reward	Environmental Rewards Observation Scale (EROS; [76])	−	+	+	+
Rumination	Perseverative Thinking Questionnaire (PTQ; [77, 78]) and Ruminative Response Scale (RRS; [79])	−	+	+	+
Distress Tolerance	Distress Tolerance Scale (DTS; [80])	−	+	+	+
Sleep disturbance	Pittsburgh Sleep Quality Index (PSQI; [81])	−	+	+	+
Chronic physical conditions	As outlined by the Australian National Health Priority Area [82, 83]	−	+	+	+

#### Intervention

The trial will use a modified version of the BATD-R manual (Activate), which involves 10 individual, weekly 60-min sessions, with a psychologist from the research team. The 10-session format allows for the inclusion of topics deemed important for the target population, and there is evidence that clinically significant improvements in depression symptoms can be achieved within this period [45]. The BATD-R manual was modified to include psychoeducation about the relationship between substance use and depression. To assist in establishing treatment goals in relation to their substance use, some motivational interviewing techniques were incorporated. Namely, this involved asking questions to elicit change talk, such as, ‘*What would you like to be different about your current situation?’* Other additions include the provision of a list of behavioural techniques for managing craving [65], and a simple breathing exercise. Given the high levels of psychiatric comorbidity among substance users in drug treatment [66, 67], self-soothing and grounding techniques have been included for managing emotional distress, and defusion exercises for the management of unhelpful thoughts. Participants may choose to withdraw from the intervention at any time, but will still be contacted for follow-up assessment, unless they have withdrawn from the study.

To encourage treatment attendance participants in Activate will receive a reminder call the day prior to each session to confirm their appointment for the following day and appointment times will be highly flexible throughout the treatment program, with the option to reschedule appointments if required. Therapists will keep logs of clients’ attendance at sessions.

The use of project therapists, as opposed to existing clinicians within treatment agencies, has been chosen to minimise the risk of contamination of the control group. In order to avoid the outcome of Activate being attributed to a single therapist bias, two clinical psychologists will be employed. Both psychologists will receive extensive training in treatment delivery, provided by the lead developer of BATD-R, [name], and will be supervised by a senior clinical psychologist with experience in the treatment of depression and substance use. The Activate treatment manual will be taken into each session by the therapist to ensure all proposed areas are covered. The therapist will also complete a session checklist, with any deviations from the therapy manual recorded in the clinical notes kept for each session. Weekly clinical supervision will be held with the chief investigators, where session checklists will be monitored. In addition, all treatment sessions will be audio-recorded to allow for assessment of treatment fidelity.

